### **Secondary objective**

The secondary objectives focusing on sleep and general feelings of fatigue on the other hand can be influenced by prior knowledge to allocation to the intervention and control. Therefore, we will include these for exploratory purposes and we will only explore whether variation in vitamin D status in both groups correlates with variations in sleep and general feelings of fatigue, instead of investigating the direct effect of the intervention in these indicators.

## **7.3 Data treatment**

### **7.3.1 General**

CG selections will send a list of names, e-mails, and addresses to the researcher at TU/e who will further inform participants ([name]). This data is shared by CG selections via their secured customer portal. The TU/e researcher responsible for informing the participants about the study and randomizing the participants ([name]) will construct an account with secured password in this portal where this data can be accessed.

After randomization, names, addresses and phone numbers of participants in the intervention group will be send from TU/e to Signify only with the goal to install the luminaire at the home of participants (in the intervention group). Participants will also receive a participant ID at the beginning of the study by the responsible researcher at the TU/e ([name]). They will use this ID to complete all online questionnaires so that no names or e-mails are logged by the questionnaire tool. DVU (responsible for the blood sampling) will also receive these participant ID's so that they can transfer the 25(OH)D serum levels to TU/e anonymously (only using the participant ID's). An encrypted file saved at the secured laptop of the TU/e researcher will contain the key regarding assigned ID numbers and participant names. This file is only accessible for the TU/e research team ([name], [name] [name], and [name]). Data from the questionnaire tool (see section 5.3.4.) and the blood samples (see section 5.3.3) will be double coded (pseudonymized) by an independent researcher

of the HTI department and will send the double coded data (without initial ID numbers) back to the investigator for the analyses ([name]). The pseudonymized full data set will be stored for at least 15 years at the encrypted TU/e server. An encrypted file with the key/link between the assigned number/code and participant ID's will be saved and stored in a secured environment at the HTI department and is only accessible to the appointed researcher and can be accessed on request by the responsible TU/e research team if needed. There will be no reporting on individual results, only on the group level (aggregated data). Pseudonymized data will only be accessible to the investigators from the TU/e (see above) and will not be shared with Signify (or any other party/researcher apart from the assigned TU/e researchers: [name] [name], [name], and [name]). Reports on the aggregated results will be shared with Signify (e.g. means, SD's, min-max values, graphs/bar charts of these values, and aggregated statistical tests to test the hypotheses).

### **7.3.2** *Data treatment of inclusion/exclusion criteria*

For the inclusion/exclusion screening, CG selections will send an email to potential participants in their participant base (see section 4.1) They will be asked to confirm whether they can be included or not based on the in- and exclusion criteria mentioned in the e-mail, without mentioning the specific reason. This prevents processing needless personal details. In case participants can and want to participate, they will sign an informed consent form provided by CG selections approving for transfer of their name, e-mail, and phone number to the responsible researcher from TU/e.

**7.3.3*****Main study parameter: Vitamin D3 serum levels***

The blood sampling procedure and serum analysis will be conducted by Diagnostiek Voor U Eindhoven (DVU) as a formally recognized health provider. DVU will send the blood sample results combined with the initially assigned Participant ID's via an encrypted e-mail to the HTI researcher who will double code (pseudonymize) this data before sending it to the data-analyst ([name]). Participants give consent for DVU sharing this data with the TU/e researcher via the consent form. No diagnosis or advice can and will be given based on the serum vitamin D3 levels. If participants have any questions regarding the gathered blood values, they can turn to their general practitioner or contact DVU. Serum 25(OH)D values will be stored for long-term at the local secured TU/e server (15 years). DVU U will destroy the actual blood samples 5 days after the blood analyses have been conducted at the laboratory. DVU will store the coded vitamin D blood values for a period of 20 years.

**7.3.4*****Secondary parameters on sleep and general fatigue***

Participants will receive a participant ID from the researcher at the TU/e which they (the participant) will use to complete the questionnaires. The online tool Limesurvey will be used to complete the questionnaires. The questionnaires on sleep and fatigue will be completed via this tool three times (baseline, measurement 1, and measurement 2). The daily presence diary (completed daily on paper) will be uploaded (scan or photo) via Limesurvey as well every week using the same participant ID. Limesurvey is a locally installed and secured tool currently used at the TU/e for conducting online questionnaire research. Data collected via this tool will only be saved locally at the secured TU/e server. Participants will only fill in their participant number and the answers to the questionnaires. No other personal data that can be tracked back to a person (e.g. names, e-mail addresses, residence, IP numbers etc.) will be probed in these questionnaires. Limesurvey data will be downloaded at the end of the study by the independent HTI researcher who will pseudonymize the data before it is sent (together with the serum 25(OH)D values) to the researcher who will conduct the analyses ([name]).

#### 7.4 Study procedures

The selection and recruitment will take place by a stepwise approach:

1. CG selections will send out an e-mail to the population base in Eindhoven and surroundings (18+) including the sum-up of the in- and exclusion criteria. Via an e-mail to CG selections, participants can express interest in participation in case they meet the in- and exclusion criteria. In the email from CG selections, participants also give consent to send personal information (name, phone number, home address) to TU/e.
2. CG selections will call participants who are interested in participating and double-check the criteria for participation via phone. Participants will give oral and written permission to CG selections to share their e-mail and phone number with the TU/e researcher ([name]).
3. If the employee has given permission to share the e-mail address with the TU/e, the TU/e will approach the employees and inform them on the procedure of the pilot study towards the effects of artificial UVB on vitamin D levels by e-mail. The participant will sign the consent form after receiving the oral instructions about the study and reading the participant information.
4. Eligible participants will be randomized to the intervention or the control group.

Before the start of the execution of the study protocol, participants who adhere to the inclusion criteria will be contacted and informed about the study by the research team and provided the opportunity to ask questions. At the end of this meeting, participants are asked to read the participant information again in their own time and send back the signed informed consent form if they decide to participate. In this consent form, participants also sign for transfer of their home address (contact details) to Signify, only with the goal to make an appointment to install the luminaire at their home office. Participants can ask any questions regarding the study via e-mail or phone before deciding to participate. Furthermore, the researcher will emphasize that it is always possible to stop at any time during the study without the necessity to explain choices, without any further consequences. After deciding (within 3-5 days after being informed by the researcher) to participate and signing the consent form, the researcher will inform the participants on which three days the data collection will occur (blood sampling and main questionnaire). Ideally, the blood sampling occurs on the same day of the week, at approximately the same time. Participants will inform the researcher at which timeslot they are available for the blood sampling, and if desired, the researcher can plan an appointment at DVU for the participant. Alternatively, participants can also make an appointment at DVU themselves (online) where they choose a time that fits in their schedule. In case enough participants meet the in- and exclusion criteria (at least 28), block randomization will be used by the responsible researcher to assign participants to the two conditions. In case there are insufficient participants who can guarantee at least 2.5 days of desk presence in the home office, participants with at least 2.5 days of desk presence will first be assigned to the intervention condition (based on timing of sending back the informed consent form) and remaining participants will be assigned to the control condition.

Participants will receive the first questionnaire via an e-mail link in the morning of the first assessment day (first blood sampling). The outcome of the first blood sample will be awaited before starting the intervention (installing the luminaire at the desk). This is done so that participants with high vitamin D levels that need medical attention ( $>375$  nmol/L, [41]) can be excluded from the study before receiving any extra UVB exposure (further increasing their vitamin D levels). Although we do not expect such high vitamin D levels, if it occurs, participants will be contacted by the responsible researcher explaining that participating is not possible due to high vitamin D levels in the first blood sampling test. Participants will also be advised to check their level again at their general practitioner to see if a medical reference is needed. In this case, other eligible participants willing to participate will be contacted to ask if they still want to participate. These can replace the participant(s) who drop out.

Installing the luminaire will be conducted by a technical employee from Signify in the homes of the 14 participants in the intervention group. These participants will receive a separate consent form from Signify in which they give written consent that they received the luminaire and that they will not try to sell or open the luminaire, or transfer any information about the luminaire to others during the study period. During the installing process, participants will receive a short explanation about the luminaire (e.g. on and off times, how to switch it off if needed) and they will receive a short manual about the luminaire.

After the installation of the luminaires, the study starts where participants in the intervention group will be exposed to the luminaire between 8:50 and 17:10 during working hours on workdays. In the weekends and between 17:11 and 8:49, the luminaire will be off. This is an automated process. Participants in the control group will not receive the intervention luminaire and only complete the questionnaires and the blood sampling.

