### 4.3 Exclusion criteria

The exclusion criteria include:

- Current pregnancy, breast feeding or a desire to become pregnant
- Having children at home aged 10 years or younger
- Having malignant skin conditions in the past or currently
- Photosensitive medical conditions or photo-sensitising drugs
- Users of medicines and/or cremes mentioning in the prescription as side effect extra sensitivity to the sun / interaction with sun exposure
- Planned use of sun beds, or sunbed use during the past 4 weeks
- Currently taking or planning to take oral vitamin D3 supplements or have been taking D3 supplements during the past 4 weeks.
- High vitamin D levels at the start of the study (>375 nmol/L) which need medical attention [41]

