## 7.2 Randomisation, blinding and treatment allocation

For a full visual overview of the allocation procedure see Figure 6. The independent agency CG selections will make a selection of eligible participants based in the in- and exclusion criteria (see sections 4.2 and 4.3). A list with eligible participants who are interested in participating in the study is mailed to the responsible researcher at the TU/e who will perform block randomization for assignment to the conditions. However, in case insufficient participants are available who work at least 2.5 days at their home office, selection for the intervention group will then be based on presence at the desk (at least 50%). This selection is believed not to influence the primary outcome parameter (25(OH)D serum levels) and as such the conclusions around the primary objective: Participants will not receive any (noteworthy, see [39]) UVB exposure (that could influence the serum 25(OH)D) unless they are allocated to the intervention group. In the statistical analysis, care will be taken to control for potential group differences in desk presence, time spent outside and vitamin D intake by food.

[figure not shown]

**Figure 6.** Allocation procedure

In addition to randomization, blinding is frequently applied to prevent that participants know they are in the control or intervention group. For this specific pilot, only 14 luminaires are available. These luminaires will be placed at the side of the participant's desk when allocated to the experimental group. As such the participant is aware that he or she will receive UVB. Blinding by reducing the sample size to 14 instead of 28 has been considered. However, to prevent that the data can be allocated (identified) to individual persons and to have sufficient power in the study, the total number of participants is estimated to be >25 in total. Since the 25(OH)D levels will not be affected by a pseudo-randomization and non-blinding strategy, it has been chosen to secure privacy of the participants and prioritize a sufficient sample size, and blinding is compromised.

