## 11. ADMINISTRATIVE ASPECTS, MONITORING AND PUBLICATION

### 11.1 Handling and storage of the data and documents

A data sharing agreement between CG selections and TU/e will be constructed regarding data sharing of participant names, phone numbers, e-mail addresses and home addresses. After a selection of participants is made based on the in- and exclusion criteria and interest to participate, participants will be contacted by the TU/e researcher for explanation of the study, participant information, and signing the consent form. All participants who signed the consent form and are allocated to one of the two groups (intervention vs. control), will receive a Participant ID with which the questionnaires are completed, and with which the serum 25(OH)D are transferred from DVU to the TU/e research team. Access to the key/link between the assigned number/code and names are saved in a secured local environment at the TU/e. An independent researcher at the Human-Technology department will pseudonymize (double code) the data received from DVU and obtained from the online questionnaires before sending these to the data-analyst. The double coding key will also be saved in a secured local environment at the TU/e. Data is not shared with, or stored at Signify. Analyses and reports are only on the group level (aggregated data) and not on the individual level. To protect privacy, coded data related to the pilot will be stored locally at the TU/e local server encrypted with a password. Data will be stored for a minimum of 15 year.

In order to prevent unnecessary data collection and unnecessary sharing the following actions are in place. For the blood sampling the participants will be in contact only and directly with medical partner DVU, who will do the blood sampling and the blood sample analysis. After 5 days of the analysis the remaining blood samples will be destroyed as medical waste. The laboratories will share the coded analysis results with TU/e. The independent researcher at TU/e pseudonymizes (double codes) the incoming data before sending the data set to the responsible investigator who will do the analyses. In this way, the researcher doing the analyses cannot identify individual participants in the final dataset. Participants can change their mind about including their data in the analysis until 24 hours after the final measurement day of the study.

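### As written, participants are allocated before the baseline blood sample and eligibility check, although the lamp waits for that result anyway

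*Protocol*

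**What the plan says.** Four parts of the protocol bear on the order of events.

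- **Who is randomised.** Section 7.2 says that the recruitment agency's list, screened by e-mail and telephone, "is mailed to the responsible researcher at the TU/e who will perform block randomization for assignment to the conditions". In section 7.4, repeated in 10.2, randomisation is step 4, directly after consent: "Eligible participants will be randomized to the intervention or the control group".
- **When the ID is issued.** Section 11.1: "All participants who signed the consent form and are allocated to one of the two groups (intervention vs. control), will receive a Participant ID". The questionnaires are completed under this ID (7.3.4), and the laboratory returns the serum results under it (7.3.3, 11.1).
- **When baseline happens.** Section 7.4: "Participants will receive the first questionnaire via an e-mail link in the morning of the first assessment day (first blood sampling". One exclusion criterion in section 4.3 can be judged only from that sample: "High vitamin D levels at the start of the study (>375 nmol/L) which need medical attention [41". The lamp then waits: "The outcome of the first blood sample will be awaited before starting the intervention (installing the luminaire at the desk". Section 10.2 has the same wait, but refers to switching the lamp on rather than installing it.
- **Replacement.** If someone is excluded on the first sample, section 7.4 has other willing eligible people contacted: "These can replace the participant(s) who drop out". Section 7.5 separately allows a new volunteer for anyone who stops before week 4. Neither section states how a replacement is allocated.

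Section 7.2 describes an open trial. Section 9 limits the primary analysis to participants with both a baseline and a final measurement.

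**The concern.** Randomisation protects the comparison only for the people who were randomised. If an eligibility check, a drop-out or a replacement falls between allocation and the first measurement, the people analysed in each arm need not be the people the random sequence put there. The risk is greater when the trial is open. Someone who learns that no lamp is coming may have less reason to give a first blood sample than someone who will receive one. Such a person has no baseline value, so under section 9 they leave the primary analysis.

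The protocol recognises that knowledge of the arm matters for self-report. It says that sleep and fatigue "can be influenced by prior knowledge to allocation to the intervention and control". Yet it contains no step that withholds the allocation until the baseline questionnaire is in.

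The exposure is avoidable. The intervention cannot start until the blood result is back, so nothing in the timetable requires allocation before that result.

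**Working it through.** **1. Order of events.**

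| Step | Where | What it implies |
|---|---|---|
| Agency screens by e-mail and phone and sends the list; researcher block-randomises | 7.2 | No blood result exists at this point |
| Consent, then randomisation as step 4 | 7.4, 10.2 | Allocation follows consent; no measurement comes between |
| ID issued to people who have consented and been allocated | 11.1 | ID comes after allocation |
| ID used for questionnaires and serum results | 7.3.3, 7.3.4, 11.1 | Baseline comes after the ID |
| First questionnaire and blood sample | 7.4, 10.2 | Baseline, so after allocation |
| Check against 375 nmol/L; possible replacement | 4.3, 7.4 | After allocation |
| Lamp starts once the result is known | 7.4, 10.2 | Last step |

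The fallback in 7.4 and 10.2, used if too few people can guarantee the desk presence, points the same way. It assigns people to the lamp by the order in which consent forms come back.

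**2. Weight of one person.** With 14 per arm (section 4.4), one loss or non-randomised replacement is 1/14 = 7.1% of an arm.

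**3. Possible shift in the primary comparison.** Suppose one person is lost from one arm before baseline, and their change would have differed by δ from the mean change of the 13 who remain. The mean of those 13 then differs from the full-arm mean by δ/14. The size of δ is an assumption. I scale it by the SD of 8.4 nmol/L in section 4.4 and compare the result with the 8.8 nmol/L difference assumed there.

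- δ = half an SD: 4.2/14 = 0.3 nmol/L, and 0.3/8.8 = 3.4%.
- δ = one SD: 8.4/14 = 0.6 nmol/L, and 0.6/8.8 = 6.8%.
- δ = two SDs: 16.8/14 = 1.2 nmol/L, and 1.2/8.8 = 13.6%.

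This is the shift per lost person. The protocol gives no rate of loss.

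**4. Effect on power.** Inputs from section 4.4: difference 8.8, SD 8.4, alpha 0.05, power 0.90. The standardised difference is d = 8.8/8.4 = 1.048. Power comes from the noncentral t distribution with n1 + n2 − 2 degrees of freedom and noncentrality d × √(n1·n2/(n1+n2)).

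- The plan's figure first: 17 per group gives noncentrality 1.048 × √8.5 = 3.05 and one-sided power 0.911. The stated 17 is reproduced as a one-sided test; a two-sided test needs 21. Section 4.4 does not state the number of sides, so both are shown.

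| Analysed | Power, one-sided | Power, two-sided |
|---|---|---|
| 14 vs 14 | 0.854 | 0.761 |
| 14 vs 13 | 0.841 | 0.744 |
| 13 vs 13 | 0.829 | 0.727 |

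One loss costs 0.854 − 0.841 = 0.013 one-sided, or 0.761 − 0.744 = 0.017 two-sided.

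**5. How often the 375 nmol/L exclusion would occur.** The modelled starting level is 66.4 nmol/L (section 4.4, Figure 2). The protocol gives no baseline SD, so the spread is an assumption. The expected number among 28 is 28 × P(value > 375).

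- Normal, SD 60: z = (375 − 66.4)/60 = 5.14, giving about 0.000004.
- Normal, SD 80: z = 3.86, giving about 0.002.
- Lognormal, coefficient of variation 0.5, 0.8 and 1.0: about 0.001, 0.07 and 0.18.

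The exclusion would therefore almost never occur, as section 7.4 itself expects. Pre-baseline drop-out is the practical route.

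**The case against.** **The order is inferred.** No sentence states that randomisation comes before the first sample. Steps 4 in 7.4 and 10.2 speak of eligible participants, and 7.4 randomises once at least 28 meet the criteria. One of those criteria needs the blood result, so a reader could place randomisation after it. Section 7.3.1 says only that the ID is given at the start of the study, section 11.1 is about data handling, and Figure 6 is not reproduced in the text at hand. This stands as a caution. However, sections 4.1 and 7.2 use the word eligible for people whom the agency has screened, and the ID rule in 11.1 cannot be followed if allocation comes later. If the later order was intended, the text still has to be corrected.

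**Knowledge of the arm at baseline.** A reader might infer that every baseline questionnaire is answered by someone who knows their arm. The protocol does not say so. Section 7.2 links awareness to the lamp being placed at the desk, which 7.4 puts after the blood result. What is supported is narrower: nothing withholds the allocation until baseline is complete.

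**Choice of replacements.** A reader might also infer that replacements are picked by hand to fill a known vacant arm. Section 7.4 says only that willing eligible people are contacted. It names no arm and no selection rule. The supported point is that no allocation rule is given. That replacement also applies only after an exclusion that is not expected, and which rests on a pre-treatment value in both arms, so it adds little bias.

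**Sleep and fatigue.** Sections 7.2 and 9 decline to test the intervention's effect on these outcomes because participants are not blinded. The models use serum 25(OH)D and measurement point, not arm, as predictors. This objection largely stands and limits the harm to those outcomes.

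**Size.** The protocol gives no number of early losses and does not show that they would differ by arm. Any stated share of an arm lost would be a guess.

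**Conclusion.** The point holds as one of sequence. Read together, sections 7.2, 7.4, 10.2 and 11.1 place allocation before the baseline questionnaire and blood sample. The 375 nmol/L check, any drop-out before the first sample and any section 7.4 replacement then fall after randomisation. There is no allocation rule for replacements and no concealment until baseline is complete.

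The demonstrable size is modest: 7.1% of an arm per person. On an assumed deviation of half to two SDs, each loss shifts that arm's mean change by 0.3 to 1.2 nmol/L, against a planned difference of 8.8. Whether any such loss occurs, and whether it differs by arm, is unknown. The benefit lies mainly in the primary serum comparison.

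This does not invalidate the design. It is a protection that costs almost nothing, in a trial already below its own calculated 17 per group, and it should be settled before anyone is allocated.

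**What to change.** In sections 7.2, 7.4, 10.2 and 11.1, set one order: consent; Participant ID; baseline questionnaire and blood sample; result received and the existing eligibility check applied; block randomisation and disclosure of the arm; lamp installation. Reword 11.1 so that the ID no longer depends on allocation. Reconcile 7.4 and 10.2 on whether it is installing the lamp or switching it on that waits for the result. Enrol any reserve, with baseline done, before randomisation, so that all 28 people randomised have a baseline value and meet every criterion.

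The cost is mainly wording. The lamp already waits for the result, so little or no delay is added. Installation appointments can be confirmed only once the result is in. Participant details should still go to the lamp installer only for those allocated a lamp, as section 7.3.1 provides; holding appointments with the installer for everyone would conflict with that. A reserve who is sampled and not needed gives blood without entering the trial. This can be avoided by sampling a reserve only if a place falls vacant before randomisation is run.

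The reordering does not prevent drop-out after baseline. It also does not settle the section 7.5 replacement of people who stop before week 4, which may happen after the lamp has started. That section needs its own rule on how a replacement is allocated and whether, and how, that person is analysed.
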